### Aim of the study

To determine the effectiveness and efficiency of small group quality improvement on professional decision-making of general dental practitioners (GDPs) concerning risk assessment in ROEs (including assigned recall intervals) and risk management of MIMs for patients (children and adults) in dental practice.

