## Intervention

### Implementation strategy

Participants in both trial arms receive a recently developed evidence-based CPG on ROE or MIM. The implementation strategy consists of one interactive IQual group meeting of approximately two to three hours with a minimum of eight GDPs each. These meetings discuss the selected intervention topic, and offer a more risk-based decision-making process guided by the CPG. Topics regarding risk management, such as identification of risk factors/indicators, preventive interventions, prognosis, monitoring, record keeping, and patient scheduling are presented. In addition, all participants receive feedback from personal and group characteristics retrieved from pre-test questionnaire and specific record forms, and are invited to make use of web-based patient risk vignettes for further individual training on risk assessment policy. These risk vignettes were developed by structured consensus procedures (modified Delphi) with expert groups consisted of acknowledged GDPs and oral surgeons in special fields. In addition, reminders (flow charts) and written patient leaflets with topical information are provided during the trial period. Flow charts comprise algorithms of decision-making aspects linked to the trial arm allocation. Depending on the allocated trial arm, participants are subjected to a set of planned interventions as described in Table 2.

**Table 2 T2:** Overview of planned interventions in groups I and II.

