### Statistical analysis

The primary analysis will be performed on an intention-to-treat-analysis. Secondly, measures will be constructed in particular algorithms to define the appropriateness in variables. Thirdly, the impact on each of the primary and secondary outcomes will be estimated separately, using random effects regression models (linear or logistic) to take into account the clustering of data. These basic models include group allocation (intervention, control), measurement timing (baseline, post-intervention), and interaction of group allocation and measurement timing (=intervention effect). Fourthly, prognostic factors for the outcome (which may be confounders) will be added to the models, like patients' recall interval preferences, which varies from those assigned by GDPs, as well as the preferences regarding the prescription of radiographs by patients/GDPs. In addition, this also accounts for GDPs and patients' preferences regarding removal versus retention of asymptomatic impacted third molars. Fifthly, a limited number of subgroup analyses will be performed, including an analysis of effectiveness in participants which performed all activities as planned, i.e., education session, online training program, and helpdesk (= efficacy analysis).

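### The adjusted models add GDP and patient preferences without limiting them to pre-randomisation values, so the adjusted estimate may not be the total intervention effect

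*Protocol article*

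**What the plan says.** The Statistical analysis section of the protocol article works in steps. The third step fits basic random effects models with arm, measurement period and their interaction, and calls the interaction the intervention effect. The fourth step extends them with factors that it calls prognostic and possibly confounding, such as patients' "recall interval preferences, which varies from those assigned by GDPs, as well as the preferences regarding the prescription of radiographs by patients/GDPs". It then says that "this also accounts for GDPs and patients' preferences regarding removal versus retention of asymptomatic impacted third molars". These preferences are the only covariates named. Nothing is said about when they are measured, or about which of the two models gives the main result.

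Other sections describe what the intervention is meant to alter. Under Aim of the study, the trial is to determine the "effectiveness and efficiency of small group quality improvement on professional decision-making of general dental practitioners (GDPs) concerning risk assessment in ROEs" and management of impacted third molars. Under Study design, the MIM intervention is directed at the choice between prophylactic removal and retention. Under Implementation strategy, GDPs receive the guideline, a group meeting, feedback, training vignettes and flow charts, and "written patient leaflets with topical information are provided during the trial period". Under Outcomes and instruments, removal versus retention and radiograph use are the primary MIM measures, bitewing prescribing is a secondary ROE measure, and GDP role perceptions, attitudes and compliance are secondary outcomes.

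**The concern.** A covariate that the intervention can change is not a confounder of a randomised comparison. If the intervention alters a GDP's preference for removal, and that preference alters what the GDP does, the preference lies on the causal path. Holding it fixed takes that path out of the estimate. What remains is closer to a direct effect, and even that reading requires that no unmeasured factor drives both the preference and the decision. The hypothesis concerns whether multifaceted implementation changes practice by any route, so the total effect is the quantity wanted.

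Because the article does not rank the basic and adjusted models, a reader could take the adjusted one as definitive. An intervention that worked by changing preferences could then look weaker than it was.

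**Working it through.** **1. Covariates set beside the intervention and the outcomes**

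| Covariate named in the fourth step | Relation to the intervention | Related outcome |
|---|---|---|
| GDP preference, removal or retention | Direct target of the MIM meeting, feedback and flow charts | Primary MIM outcome |
| GDP preference, radiographs | Part of the risk-based decision-making being taught | Primary MIM outcome (radiographs); secondary ROE outcome (bitewings) |
| Patient preference, radiographs and removal | May shift through the leaflets | As in the two rows above |
| Patient preference, recall interval | May shift through the leaflets | Primary ROE outcome |

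No GDP preference on recall is named.

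**2. Timing**

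The Data collection section has information gathered before randomisation and again at the end of the trial. Registration forms are completed in each period. The article does not say that the same patients are registered twice. If patient preferences are taken from the forms, a post-intervention record carries a preference recorded after the intervention. GDP preferences could come from the first questionnaire, which covers attitude, or from later forms. The article leaves this open, so post-intervention measurement is an inference from the two registration periods.

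**3. The plan's own figure**

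Inputs from Sample size: 20% against 40%, alpha 0.05 (taken as two-sided), power 80%, ICC 0.03, three groups per arm. The usual two-proportion formula with pooled variance and no continuity correction gives n = 82 per arm before clustering. Registrations per group: m = n(1 − ICC)/(k − n × ICC) = 82 × 0.97/(3 − 82 × 0.03) = 79.54/0.54 = 147.3, against the stated 150. At 150 the design effect is 1 + 149 × 0.03 = 5.47, the effective size is 450/5.47 = 82.3 per arm, and power is 80.5%. The figure reproduces and is not altered by this point. It supplies the 20-point effect used next.

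**4. Illustration of the mechanism**

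The share s of the effect that runs through preferences is assumed, because the documents give nothing from which to estimate it. On the risk-difference scale, with no interaction and no unmeasured common cause of preference and decision, the adjusted effect is 20 × (1 − s) points.

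A large-sample simulation checked this, with 1,000,000 records per scenario, no clustering, and a linear model with arm, period and their interaction. Further assumptions: 30% hold the guideline-concordant preference without the intervention, and holding it raises the outcome probability by 0.5. The intervention raises that 30% by s × 0.2/0.5, that is 10, 20 or 30 points for s = 25%, 50% or 75%.

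| Assumed share s | Without preference | With post-intervention preference | With preference unaffected by the intervention |
|---|---|---|---|
| 0% | 0.20 | 0.20 | 0.20 |
| 25% | 0.20 | 0.15 | 0.20 |
| 50% | 0.20 | 0.10 | 0.20 |
| 75% | 0.20 | 0.05 | 0.20 |

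The loss comes only from a preference that the intervention has changed. An unaffected preference costs nothing. The primary outcomes are treated as dichotomous in the sample size calculation, and for such outcomes the article allows logistic models. There the simple (1 − s) rule does not carry over, because odds ratios also change on adjustment through non-collapsibility. The table shows the mechanism and is not a forecast.

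**The case against.** The strongest reply is that the effect is already defined and estimated before any preference enters. This stands: the third-step model gives an unadjusted total effect. A reader might infer that the trial's result as such is biased, or that a true 20-point change will be reported as 15 to 5 points. The documents support neither. The problem is confined to the adjusted models, and the range rests on an assumed share.

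A second reply is that timing is not stated and is often left to a full protocol or analysis plan. This stands in part. Harm requires values recorded after the intervention and changed by it, and the article does not say that this is what will be used. But the article goes further than leaving detail open: it names a specific covariate set, justifies it as possible confounding, and sets no limit on timing, while describing the same decisions as the target of the intervention.

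A third reply is that chance imbalance is likely with three groups per arm, so prognostic adjustment is sensible. That is right, and it would be too strong to say that preferences could never be used. The argument supports adjusting for pre-randomisation values. It does not extend to variables that the intervention can move.

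Two further readings go beyond the text. One might suppose that the models adjust for GDPs' own recall preferences; for recall, only the patients' are named. One might also take the patient's recall preference as almost a restatement of the primary ROE outcome, since it is contrasted with the assigned interval. The clause says only that the two differ, and the outcome is whether the interval suits the risk profile. For patient preferences generally, the mediator argument is weaker than for GDP preferences: the leaflets are described as informative, with no statement that they aim at preferences, and some of the variation may be case-mix.

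**Conclusion.** The point holds for the fourth-step models only. As written, they may include GDP preferences on radiographs and removal that the intervention aims to change, and patient preferences that the leaflets may shift. Where these are recorded after the intervention, the adjusted arm-by-period term can no longer be read as the total intervention effect. Attenuation is the probable direction but is not certain, and its size cannot be derived from the documents. The conclusion rests on two assumptions: that at least some preferences are taken from post-intervention records, and that the intervention moves them. The basic model and the sample size are unaffected. The plan should correct this, since the article does not say which model carries the main conclusion.

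**What to change.** Amend the Statistical analysis section in three respects:

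- State that the basic model (arm, period, arm by period) gives the main effect estimate.
- Restrict adjusted models to covariates the intervention cannot change, such as patient age, GDP and practice characteristics, and GDP attitudes from the questionnaire completed before randomisation. Exclude preferences recorded after the intervention. Exclude also risk profiles that GDPs assess after the intervention: by then the ROE-arm GDPs have been trained in risk assessment, and the profile defines whether a recall interval counts as appropriate.
- Label any model containing post-intervention preferences as an exploratory mediation analysis.

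The cost is a few sentences. The first questionnaire already covers aspects of attitude, so no new data collection is foreseen, although the article does not show whether its items yield a usable score for each topic. The small downside is less adjustment for chance imbalance in patient preferences, which matters somewhat with only six clusters.

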## Economic evaluation

An economic evaluation is performed to estimate the cost-effectiveness of the implementation intervention. This study takes a healthcare perspective and a time horizon that is similar to the implementation trial.

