## Background

Routine oral examination (ROE) refers to periodic monitoring of the general and oral health status of patients. The main purpose of ROEs is to prevent the onset of oral diseases and/or prevent further progression. This allows the introduction of preventive interventions at the appropriate time, and reduces the need for operative interventions. In most developed Western countries, a decreasing prevalence of oral diseases underpins the need for a more individualised approach in assigning individualised recall intervals for regular attendees instead of systematic decision-making of fixed intervals. In The Netherlands, about 80% of the population regularly visits the dentist for a check-up about every six months [1]. This implies that many healthy individuals are scheduled for routine oral screening. In 2000, 50% of the Dutch GDPs assigned all their regular patients for ROE twice a year [2], irrespective of level of risk for oral disease. The efficiency of this systematic monitoring system is still disputed in The Netherlands, as well as internationally [3-10]. Recently, two systematic reviews [11,12] and a clinical practice guideline (CPG) advocated an individualised risk-based assessment strategy, given the lack of good scientific evidence [13]. In addition to the debate over the frequency of ROE, GDPs also question from a quality-of-care perspective the effectiveness of the widespread prophylactic removal of mandibular impacted asymptomatic third molars (MIM) in adolescents and adults [14-16].

Recent implementation studies in medical care indicate that evidence on the effect of single interventions is mixed [18,19]. It is as yet unclear how quality of oral care in dental practice can be improved. Research data on effectiveness of interventions to promote continuing professional development for dentists are rare [17]. A previous study showed that small group education sessions did not change dentists' clinical behaviour [20]. The aim of the present study is to evaluate whether a multifaceted strategy can enhance oral health care according to evidence-based dental practice. Consensus-based CPGs on ROEs [13] and on the management of MIMs [20] are available for educational purposes in clinical practice.

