**Secondary MIM-outcome**	Professional attitudes/compliance and feedback: Interviews of patients (17–35 years of age) to confirm risk-based performance.	**Questionnaire**

• For high-risk children and adolescents (0 to 18 years), recall intervals of less or equal than seven months should be assigned. For those with a low-risk profile, an assigned recall of more than seven months is considered appropriate.

• For high-risk adults (18 years and older): recall intervals of less than nine months should be assigned. For those with a low-risk profile, an interval of nine months or longer is considered appropriate.

The secondary outcome measures for the ROE arm are:

1. The use and appropriateness of individualised risk-based assessment in prescribing bitewing radiographs (BWs) in months. The appropriateness will be assessed as follows:

• For high caries-risk children and adolescents (0 to 18 years): BW frequencies of less than 24 months are determined as appropriate; for those with a low-caries risk profile, BW frequencies equal or more than 36 months.

• For high caries risk adults (18 years and older): BW frequencies less than 36 months are determined as appropriate; for those with a low-caries risk profile, BW frequencies of equal or more than 48 months.

2. The use and appropriateness of individualised communication/feedback and advice in patients with a periodontal risk DPSI-score >1, and present dental caries experience. The appropriateness will be assessed as the proportion of patients per GDP receiving appropriate preventive advice/feedback will be calculated. Furthermore, as a secondary outcome measure, professional role perceptions and compliance concerning the recommendations of the ROE-CPG is assessed by means of questionnaires provided at the beginning and end of the study.

3. Resource use will be documented for an economic evaluation:

• The type of recall interval (months) per GDP over the past 3 years

• BW radiographs and other types of radiographs per GDP over the past 3 years

• Type of performer of ROEs: GDP versus oral hygienist/dental auxiliary

• Additional interventions per GDP (i.e. polishing stains/removing dental calculus) encompassed at ROEs over the past 3 years.

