### Costs

Costs considered are those used for the implementation (time for participation by GDPs, preparation time, use of materials) and for changes (if any) in professional performance (recall intervals between successive ROEs, total number of radiographs, both based on individual risk assessment). Oral care unrelated to the topic of the interventions within the observed time period will not be considered. Resource use will be extracted from trial data, where possible, or collected separately for the purpose of the economic evaluation. Costs will be valued according to prevailing Dutch guidelines for economic evaluations, and alternatively according to the current national fee-coding list for individual oral treatment procedures in general dental practice.

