### Timeframe of the study

We plan to randomise six of the initially recruited IQual groups that have declared their willingness to participate in this study, and to assign them randomly to one of the two intervention arms. The baseline data collection will take place at the beginning of the study during months one and two. The intervention will start in months two and three, and follow-up data collection will be collected in months eight through ten. The scheduled time for the trial is estimated to be seven to ten months (Appendix 1), assuming that each GDP will collect data from at least 20 regular attending patients by means of the trial registration form.

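### The trial-length economic horizon charges the whole one-off implementation cost but credits only a small part of the saving from longer recall and bitewing intervals

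*Protocol article*

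**What the plan says.** The Economic evaluation section fixes the horizon: "This study takes a healthcare perspective and a time horizon that is similar to the implementation trial". Timeframe of the study gives its length: "The scheduled time for the trial is estimated to be seven to ten months". The same section sets the order of events: "The intervention will start in months two and three, and follow-up data collection will be collected in months eight through ten".

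Under Costs, two components are counted. One is the implementation itself (dentists' participation time, preparation, materials). The other is any change in professional performance, described as "recall intervals between successive ROEs, total number of radiographs".

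Under Effectiveness, the effect is professional performance, taken from the trial outcomes. Health outcomes are declared out of scope.

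The intervals that would produce savings are in the ROE study section. For adults: "For those with a low-risk profile, an interval of nine months or longer is considered appropriate". For children and adolescents: "For those with a low-risk profile, an assigned recall of more than seven months is considered appropriate". For bitewings in low-risk adults the criterion is "BW frequencies of equal or more than 48 months", and for low-risk children and adolescents it is 36 months or more. The Background gives usual practice: "about 80% of the population regularly visits the dentist for a check-up about every six months".

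The Analysis subsection plans an ICER for each clinical topic, one-way sensitivity analyses of the most influential factors, and a bootstrap of observed cost-effect pairs. It names no longer-horizon scenario.

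**The concern.** The two cost components run on different clocks. The implementation cost is incurred once, near the start, and is counted in full however short the horizon. The offset accrues slowly, because a longer recall interval saves money only when a visit that would have taken place does not, and a longer bitewing interval only when a radiograph falls away. With recall of nine months or longer and bitewing cycles of 36 to 48 months or more, a window of 5 to 8 months after the intervention sees little of that offset.

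Efficiency is part of both the stated aim and the hypothesis. If the numerator of the ROE ICER holds all of the outlay and a small part of the offset, the incremental cost may be overstated because of the cut-off alone. Resampling observed pairs cannot recover savings that arise after observation ends.

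**Working it through.** The protocol article gives no cost, visit count or ICER, so there is no figure of its own to reproduce on this point.

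**Inputs from the article.** Intervention at month S = 2 or 3 and follow-up in months 8 to 10 (Timeframe of the study). Usual recall about 6 months (Background). Low-risk adult recall of at least 9 months, and low-risk bitewing intervals of at least 36 months (children and adolescents) or 48 months (adults) (ROE study). Target effect of 20 percentage points (Sample size).

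**Assumptions made here.** Every switched patient moves from 6 to exactly 9 months at the first visit after the intervention. That visit falls evenly over the next 6 months. The three-year comparison period is illustrative and is not in the article.

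**1. Length of the window.** Shortest: 8 − 3 = 5 months. Longest: 10 − 2 = 8 months.

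**2. Realised visits saved inside the window.** With F months of follow-up and first visit at time t, the old schedule gives a further visit if t + 6 ≤ F. The new one gives none, because t + 9 exceeds F for every F up to 8. The saving per switched patient is therefore max(0, F − 6) / 6.

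| F (months) | Visits saved |
|---|---|
| 5 | 0 |
| 6 | 0 |
| 7 | 1/6 = 0.17 |
| 8 | 2/6 = 0.33 |

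A visit merely deferred beyond the cut-off counts here as wholly saved, so the count is not unkind to the plan.

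**3. Steady-state costing from assigned intervals.** The yearly saving is 12/6 − 12/9 = 2.00 − 1.33 = 0.67 visits. Over 5 months: 0.67 × 5/12 = 0.28. Over 8 months: 0.67 × 8/12 = 0.44.

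**4. Illustrative three years.** At the steady-state rate: 3 × 0.67 = 2.0 visits. Counting realised visits to study month 36 under the assumptions above:
- S = 2: first visits leave 28 to 34 months. The old schedule gives on average (2 × 4 + 4 × 5)/6 = 4.67 further visits and the new one 3, a saving of 1.67.
- S = 3: 27 to 33 months remain. The old schedule gives (3 × 4 + 3 × 5)/6 = 4.5 and the new one 3, a saving of 1.5.

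**5. Share captured.** Realised visits: from 0 up to 0.33/1.67 = 20%. Steady-state costing: 0.28/2.0 = 14% to 0.44/2.0 = 22%. The implementation cost is captured at 100% throughout.

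**6. Per patient at the target effect.** If all 20 points were 6-to-9-month switches, the within-window realised saving is 0.20 × 0 = 0 to 0.20 × 0.33 = 0.07 visits per patient. Over 36 months it is 0.20 × 1.5 = 0.30 to 0.20 × 1.67 = 0.33. The ICER denominator is 20 points in both cases.

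**7. Bitewings.** The window covers 5/48 = 10% to 8/48 = 17% of one 48-month cycle, and 5/36 = 14% to 8/36 = 22% of a 36-month cycle.

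**The case against.** **The effect is not truncated.** A reader might infer that full cost is set against almost no effect, so that the efficiency question cannot be answered. The Effectiveness subsection rules this out: the effect is guideline adherence, fully observed at follow-up. Cost per unit of adherence can be estimated on this horizon. This objection stands, and it confines the point to the numerator.

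**Some savings do fall inside the window.** A reader might infer that visits are saved only after the horizon ends. They are not: the visit skipped is the one due six months after an early post-intervention visit, and up to a third of switched patients could skip it in time. At 8 months, the realised saving is 0.33/0.44 = 75% of the steady-state accrual for that period.

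**The costing basis is not stated.** Costs are tied to recall intervals, and the assigned interval is the primary ROE outcome, so costing assigned intervals is a natural reading. It narrows the problem without removing it, because a trial-length window then credits 0.28 to 0.44 of about 2.0 visits. The resource list in the ROE study section points another way, to use over the past three years. Collected at follow-up, only 5/36 = 14% to 8/36 = 22% of that period would follow the intervention.

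**The three-year comparison is a choice.** Eight months is 22% of 36 by construction. True, but the asymmetry remains: the implementation cost does not shrink with the horizon and the offset does.

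**A within-trial horizon is openly declared and avoids extrapolation.** This stands, and is why that analysis should be kept. The sensitivity analyses might be meant to include the horizon, but the text does not say so.

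**Conclusion.** The point holds for the cost numerator of the ROE ICER only. The horizon counts the whole one-off cost and only a small part of the downstream saving: 0 to 0.33 realised visits per switched patient, or 0.28 to 0.44 at the steady-state rate, against about 1.5 to 2.0 over three years. Bitewing savings are cut off at least as early relative to their cycle. Incremental cost may therefore be overstated.

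A reader might go further and conclude that the ROE intervention will look cost-increasing. The article does not support that. It gives no implementation cost, fee or number of patients per dentist, and one meeting may influence decisions for many patients. Nor does every change save money, since appropriate recall for high-risk patients can mean shorter intervals.

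The figures rest on six-month usual recall (a population statement), evenly spread visits, a uniform 6-to-9-month switch, and a three-year period chosen for illustration. The threshold for low-risk children is lower, so the saving per switched child may be smaller. The third-molar ICER was not examined.

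**What to change.** Three changes to the Economic evaluation text:

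1. Keep the within-trial ICER as declared.
2. State that ROE cost offsets are calculated from the assigned recall and bitewing intervals already recorded, as expected numbers per patient-year (12 / assigned months). This also counts added visits where intervals are shortened.
3. Add a pre-specified longer-horizon scenario, for example three to four years, with the implementation cost spread over that period and a sensitivity analysis in which the effect wanes.

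No new data are needed; the cost is wording and a simple calculation. The drawback is that the scenario assumes assigned intervals are kept and the effect persists, neither of which the trial observes. It should therefore be reported alongside the within-trial result and not replace it.
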